## Abstract

Intubated critically ill patients are susceptible to secretion accumulation because of compromised airway clearance. Various airway clearance interventions are employed to prevent complications arising from mucus retention. This Delphi study aims to collect global opinions in an international expert panel of ICU professionals on the usefulness of these various airway clearance interventions. A steering committee performed a literature search informing the formulation of statements. Statements are grouped into two distinct parts: (1) Humidification and Nebulization, and (2) Suctioning and Mucus mobilization techniques. For each part, a diverse panel of 30–40 experts will be selected, with concerted effort to involve experts from various medical specialties involved in airway clearance methods. Multiple choice questions (MCQs) or 7-point Likert-scale statements will be used in the iterative Delphi rounds to reach consensus on various airway clearance interventions. Rounds will continue until stability is achieved for all statements. Consensus will be deemed achieved when a choice in MCQs or a Likert-scale statement achieves ≥75% agreement or disagreement. Starting from the second round of the Delphi process, stability will be assessed using non-parametric χ^2^ tests or Kruskal–Wallis tests. Stability will be defined by a *p*-value of ≥0.05.

## 1. Introduction

Intubated critically ill patients often need airway clearance interventions due to the risk of secretion accumulation [1,2,3]. Frequently used airway clearance interventions are endotracheal suctioning [4,5] and subglottic drainage [6], active and passive humidification of inhaled air [7,8,9], nebulization of various agents to reduce the viscosity of mucus present in the airways [10], gravity-assisted drainage techniques [11], oscillatory techniques [12] and chest-wall compressions [13], and cough techniques [14,15,16]. This variety of airway clearance interventions are currently employed with inconsistent frequency to prevent complications arising from mucus retention.

The practice of airway clearance interventions varies widely with different criteria to initiate or cease the abovementioned interventions [17,18,19], and some of them are even used routinely, in all intubated critically ill patients without a clear clinical indication [17,18,19,20,21,22,23,24,25]. It should be noted that despite having potential benefits, some if not all interventions may have adverse effects [14,26] or may cause pain or discomfort [27,28], and some will increase medical waste [29]. There is a clear lack of high-quality recommendations regarding the use of airway clearance interventions. Available guidelines are mostly derived from clinical expertise in combination with low-level evidence [4,10]. At present, there is no international consensus concerning the practice of airway clearance interventions.

This protocol for an upcoming Delphi study aims to gather global opinions of ICU professional experts on the usefulness of airway clearance interventions in intubated critically ill patients. The document begins with a detailed description of the various airway clearance interventions and concludes by outlining the methods to be used in the planned Delphi study.

### 1.1. Airway Clearance Interventions

#### Endotracheal Suctioning

Suctioning is the most common method for clearing the airways of intubated critically ill patients and various techniques are employed [4,30]. Endotracheal suctioning can be performed using either an open or closed approach [30]. Open suctioning involves disconnecting the patient from the ventilator and using a single-use sterile catheter to remove mucus. In contrast, closed suctioning keeps the ventilator connected, minimizing the loss of airway pressures and reducing the risk of airway contamination. While open suctioning uses single-use suction catheters, closed suctioning catheters can be used for several days, which may reduce hospital waste.

Considerable uncertainty persists regarding the optimal approach to endotracheal suctioning and its impact on patient outcomes [31]. The debate between open and closed suctioning methods remains unresolved, with differing views on their respective benefits and risks. Additionally, there is ongoing discussion about the ideal frequency and best practices for minimizing potential complications associated with airway suctioning.

### 1.2. Subglottic Drainage

Subglottic drainage is employed to remove secretions that accumulate above the cuff of the endotracheal tube, an area that endotracheal suctioning cannot effectively reach [6]. This technique requires a specialized endotracheal tube with an additional lumen for continuous or intermittent suctioning. By removing these secretions, subglottic drainage prevents the aspiration of secretions into the lower airways. Even without these specialized endotracheal tubes, the removal of secretions through oropharyngeal suctioning before patient re-positioning may assist in preventing VAP [32].

However, questions persist about the broader applicability of the use of subglottic endotracheal tubes and their effectiveness. It is unclear whether these outcomes can be reliably replicated in diverse populations or across various clinical environments.

### 1.3. Humidification

Two methods are used to optimize inhaled air humidity: active humidification with a heated humidifier (HH) and passive humidification with a heat and moisture exchanger (HME) [7]. The HME filter retains heat and moisture during exhalation, passively humidifying inhaled air, while HH actively heats and moistens the air through a device in the ventilation circuit, resulting in higher humidity [8,9]. Currently, health professionals choose the humidification type based on clinical reasoning, with HH being costlier but preferred for prolonged ventilation [21,33].

Although both active and passive humidification methods are widely used, there is a lack of robust evidence guiding the choice between them. Additionally, the best humidification strategy for different patient populations remains a topic of debate, particularly concerning the prevention of complications like airway obstruction or infection.

### 1.4. Nebulization Therapy

Nebulized mucolytic agents are commonly used in ventilated patients to reduce mucus viscosity, whereas bronchodilators may aid clearance by widening small airways [10]. Nebulized agents are administered through a device that converts liquid medication into a fine mist or aerosol that can be inhaled directly into the lung [25].

The routine use of nebulization therapy of mucolytics and bronchodilators in invasively ventilated patients did not prevent accumulation of airway secretions in the endotracheal tube [26]. Moreover, the effects of nebulization therapy on clinical outcomes are still unclear. The decision to use these agents involves weighing their perceived benefits for mucus clearance against the risks of side effects, underscoring the importance of defining their role in the care of ventilated patients.

### 1.5. Gravity-Assisted Drainage Techniques

Gravity-assisted drainage can enhance mucus mobilization by promoting the cephalad movement of mucus towards larger airways, potentially improving the effectiveness of various airway clearance interventions. Prone positioning, recommended for patients with moderate to severe acute respiratory distress syndrome, may be particularly effective in promoting mucus movement towards larger airways and into the endotracheal tube, where it can be easily removed through suctioning [34].

The degree to which these interventions improve mucus mobilization and aid airway clearance, especially when used alongside other techniques, remains uncertain, as does their impact on clinical outcomes.

### 1.6. Oscillatory Techniques

High-frequency chest-wall oscillation (HFCWO) using an external vest rapidly compresses and relaxes the chest wall, which can enhance expiratory flow and improve mucus clearance by moving secretions cephalad [12]. HFCWO is predominantly used in non-intubated patients with hypersecretory conditions like cystic fibrosis and bronchiectasis, but it may also be beneficial in intubated critically ill patients.

The potential risks and clinical benefits of HFCWO in intubated patients, along with the subgroups most likely to benefit and the criteria for selecting, remain uncertain.

### 1.7. Chest-Wall Compressions

Chest-wall compressions, including vibration and percussion, are manual techniques used to mobilize secretions in invasively ventilated patients, moving them from peripheral to central airways [13]. These interventions are currently recommended for patients with a weak cough response to suctioning, and for patients with thick, tenacious airway secretions.

Evidence for the effectiveness of these interventions in invasively ventilated patients is limited. Questions remain about the optimal frequency, duration, and technique, as well as their impact on clinical outcomes.

### 1.8. Manual/Ventilator Hyperinflation and Mechanical Insufflation–Exsufflation

With manual hyperinflation (MH), the patient is temporarily disconnected from the ventilator, and a greater than normal tidal volume is manually inflated using a resuscitation bag with a slow inspiratory flow. This is followed by an inspiratory pause and a rapid release of the built-up airway pressure, which generates a high peak expiratory flow and aids in the movement of secretions. MH mimics a natural cough and helps prevent atelectasis [14].

The same technique can also be delivered through the mechanical ventilator, termed ventilator hyperinflation (VH), without the need for the disconnection of the patient from the ventilator and provides a potentially more accurate means to deliver the known pressure and/or tidal volume delivery during the intervention [15]. Mechanical insufflation–exsufflation (MI-E) devices, also known as cough-assist devices, provide a controlled artificial cough by delivering a predefined positive pressure followed by negative airway pressures. MI-E may be a more effective alternative to airway suctioning alone or MHI or VHI in certain situations as a means of mobilizing airway secretions [16], such as in patients with respiratory muscle weakness.

MH/VH are effective in improving mucus clearance over and above airway suctioning alone; however, their impact on clinical outcomes is uncertain, with concerns about risks like lung overdistension and hemodynamic instability. The use of MI–E in intubated patients is less studied than in non-invasive settings, leaving limited data on its safety and benefits. Potential risks, such as barotrauma, desaturation, intercranial hypertension, and hemodynamic instability, add to the uncertainty of its role in critically ill patients.

### 2.2. Objectives

To review and structure existing evidence on the effectiveness of airway clearance interventions in intubated critically ill patients;To collect global opinions on the usefulness of these various airway clearance interventions in invasively ventilated ICU patients.

This Delphi will be conducted in two separate parts. This division is necessary because the Delphi process consists of two distinct parts: (1) Humidification and Nebulization, and (2) Suctioning and Mucus mobilization techniques. The latter includes endotracheal and subglottic suction, gravity-assisted drainage techniques, oscillatory techniques, chest-wall compressions, and cough techniques. Each part focuses on different aspects of the topic and will be completed by mostly different panellists with specific expertise relevant to the respective areas. Presenting the results separately will allow for a more focused and clear discussion of the outcomes from each part, ensuring that the insights are tailored to the unique contributions of each group of experts. To ensure a representative selection of experts, a structured selection survey will be used to identify and invite professionals with the appropriate knowledge and experience in each domain. The selection survey will be used to determine whether experts contribute to both parts of the Delphi process or only one, depending on their specialization. The overall project timeline for both parts of the Delphi study is anticipated to be between 12 and 15 months.

### 2.3. Expert Panel

An international expert panel of at least 35 to 40 healthcare professionals representing ICU-nurses, respiratory therapists (or comparable versions, based on local implementation), physiotherapists, speech and language therapists, ICU-physicians, and pulmonologists with expertise in the field of invasively ventilated ICU-patients will be selected based on the following criteria:○At least 5 years of clinical experience, with care for invasively ventilated patients (teaching and non-teaching);○Participation in the development of a guideline or authorship of at least one paper on airway care for invasive ventilated patients in an international peer-reviewed journal;○No more than 70% of the panellists from each sex, and from each of the high-, low-, and middle-income countries;○Has a good command of the English language.

Purposive sampling will be utilized to recruit panellists by reviewing recent publications in the field of airway care for invasive ventilated patients. Selection of panellists will be guided by predefined criteria, with deliberate efforts to ensure a balance in gender and geographical representation. Panellists will receive an invitation in English via email detailing their role, the study’s objectives, and the Delphi process. Those who accept the invitation will participate in the Delphi rounds, with ongoing communication and regular progress updates provided to encourage their continued involvement. These updates will be provided in Delphi round reports after each round. To minimize dropout rates, at least three reminder emails will be sent during each round, and any feedback or concerns regarding the process will be addressed. Additionally, a schedule of Delphi rounds (each lasting 2 weeks) will be adhered to in order to maintain continuity.

### 2.4. The Delphi

#### 2.4.1. Step 1: Formulate List of Domains

In three consecutive meetings, the members of the steering committee discussed the airway clearance interventions to be included in this study. It was decided that the following interventions should be addressed:○Endotracheal suctioning and subglottic drainage;○Humidification;○Nebulization;○Mucus mobilization techniques.

Additionally, it was decided that the Delphi should provide information on the following:○Indications and contraindications;○Safety;○Effectiveness;○Efficiency;○Involvement of healthcare professionals.

#### 2.4.2. Step 2: Literature Search and Formulation of Statements

The steering committee conducted a literature review in the Medline database (PubMed) on airway clearance interventions in intubated critically ill patients, and selected studies if

○One of the above airway clearance interventions was tested;○They were a randomized clinical trial;○They regarded safety, effectiveness, or efficiency;○They were published in or after the year 2000.

Studies were excluded if

○They were performed in non-adults;○They were not a clinical study;○They did not address the outcomes of interest.

The PRISMA flow diagram will be used to depict the process of identifying, screening, and selecting studies for inclusion [38]. The available evidence, or the absence thereof, will guide the formulation of statements and questions for the domains included in the first Delphi round.

#### 2.4.3. Step 3: Preparation of the First Delphi Round

The panellists will receive a Delphi questionnaire via Google Forms, containing a series of questions related to the specified domains. Throughout the Delphi process, the identities and responses of the panellists will remain anonymous. Panellists will be asked to complete the questionnaire based on their knowledge and expertise in the subject area. The questionnaire will include multiple-choice questions (MCQs) and statements with a 7-point Likert scale. Responses and comments from panellists will be summarized into a report and provided as synthesized feedback in the following survey round.

#### 2.4.4. Step 4: Subsequent Delphi Rounds

The steering committee will evaluate the results of each round through online meetings. Statements will be revised, removed, or added as necessary, based on the feedback, comments, and responses received by the panel, The revised and remaining statements will be continued through subsequent rounds until a stable consensus or dissensus is reached (defined as ≥75% agreement or disagreement on a Likert scale and selected options in an MCQ). A summary of the results from each round will be shared with the panellists, and the survey process will be repeated using the updated questionnaire. The Delphi rounds will continue until the responses stabilize, with no more than 10% of panellists providing feedback that requires further adjustments. The process will be repeated until stability is achieved for all statements.

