### 2.6. Analysis Plan

A descriptive analysis of each survey round will be performed. The stability of the responses will be analyzed from the second round onwards using the non-parametric Chi-square test or Kruskal–Wallis test. To define the stability of statements, a *p*-value of ≥0.05 will be interpreted as a lack of stability. Consensus will be defined when a choice in the MCQ or Likert-scale question has at least 75% of the votes from panellists. For the Likert-scale, the answering options are divided into disagreement (1 to 3), neutral (4), and agreement (5 to 7): 1 for strongly disagree, 2 for somewhat disagree, 3 for disagree, 4 for neutral, 5 for somewhat agree, 6 for agree, and 7 for strongly agree. Stability is assessed after two consecutive rounds of answers defined as consensus or dissensus. All data will be analyzed, regardless of the completeness of answers.

The steering committee will compile the results from each Delphi round and share them with the panellists, together with the survey of the following round. These results will demonstrate the degree of consensus or dissensus achieved for each statement. In the final results, percentages of voting for each answering option will be reported.

The findings from this study will be presented in two separate reports: (1) Humidification and Nebulization, and (2) Suctioning and Mucus mobilization techniques.

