Our Delphi study has strengths. The Delphi study will be groundbreaking in its evaluation of airway clearance interventions across a wide range of techniques specifically in intubated, critically ill patients. By following a rigorous and methodologically robust Delphi, our study will provide clarity and guidance on the best practices in this vulnerable group of patients. We aim to recruit a diverse panel of experts from various geographical regions, representing both resource-rich and resource-limited settings to ensure a broad range of perspectives. This panel will consist of a multidisciplinary group of professionals, including ICU nurses, respiratory therapists, physiotherapists, intensivists and pulmonologists, and other healthcare professionals in equivalent roles based on local practices as long as they have expertise in the care of invasively ventilated ICU patients. In addition, we will ensure gender and age balance within the panel to provide a wide representation of views and experiences. By including this diverse range of professionals, our study will capture broader insights into regional practices and resource availability, making the results widely applicable. Selection of the panellists will be based on predefined criteria and a self-assessment survey to ensure the inclusion of individuals with relevant experience and knowledge in airway clearance interventions. To avoid the influence of peer or group bias, expert responses will remain anonymous throughout the Delphi rounds, allowing participants to provide their opinions independently and without peer pressure. The final consensus will emerge through several iterative rounds, with the endpoint being reached when responses show stability across all statements.

This study will also have limitations. One potential challenge is that the interpretation of statements may influence panellists’ responses. However, this will be mitigated by incorporating open feedback from panellists in each round and assessing the consistency of responses over multiple iterations. Another limitation could arise from differences in local practices or access to certain airway clearance techniques, which may affect responses. To address this, we will limit the panellists from any single geographical region to no more than approximately one-third, ensuring a well-balanced global perspective and providing the published literature on the different techniques.

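### Stability is tested without requiring identical wording in the two rounds, so a substantively reworded statement can close as stable after one vote on its final text

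*Protocol article*

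**What the plan says.** Section 2.4.4 of the protocol article lets the steering committee change the items after every round: "Statements will be revised, removed, or added as necessary, based on the feedback, comments, and responses received by the panel". It then gives changed and unchanged items the same closing rule: "The revised and remaining statements will be continued through subsequent rounds until a stable consensus or dissensus is reached". Consensus or dissensus is set there at 75% or more agreement or disagreement.

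Section 2.6 gives the stability test, a chi-square or Kruskal–Wallis test: "The stability of the responses will be analyzed from the second round onwards". It adds: "Stability is assessed after two consecutive rounds of answers defined as consensus or dissensus". Section 2.4.5 builds the final panel statements from the results of the last round found to be stable.

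The Discussion accepts, as a limitation, that "the interpretation of statements may influence panellists’ responses". The mitigation it offers is open feedback in each round together with a check of how consistent the answers are over rounds.

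The direction of the test is given twice and differently. The Abstract takes p≥0.05 as stability ("Stability will be defined by a" p-value of that size). Section 2.6 says that the same p-value "will be interpreted as a lack of stability".

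**The concern.** A stability test asks whether a panel gives the same answer when asked the same question again. If the statement was reworded in between, the two rounds answered different questions. A non-significant result then says nothing about whether the new text would be answered the same way twice, and a significant one cannot separate a wording effect from a change of opinion.

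Three things are absent from the stated rules: that the compared rounds must share their wording, that a revision restarts the stability count, and that a revised statement counts as new. A statement reworded after round 1 can therefore be declared stable in round 2 and published as such, although the panel voted on that text once. For such a statement, consistency over rounds, half of the mitigation that the Discussion offers for wording effects, is not being measured.

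**Working it through.** **What the rules allow.**

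1. Items may be reworded after round 1 (2.4.4).
2. Reworded items continue with the others under the same closing rule (2.4.4).
3. Stability testing starts in round 2 (2.6). A test in round 2 has only round 1 to compare with. For an item reworded after round 1, that is the old wording. This step is an inference, because 2.6 does not name the comparator.
4. Nothing in 2.4.4 or 2.6 makes identical wording a condition.

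A reworded item can thus satisfy the closing rule in round 2, on its first vote.

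**How often this could happen.** The article gives no power or error rate for the stability test, so there is no figure to reproduce. The following is an illustration.

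Inputs from the article:
- consensus threshold 75% (2.4.4 and 2.6);
- p≥0.05 taken as stable (Abstract);
- panel size n = 30, 35 and 40. The Abstract gives 30–40 per part and section 2.3 gives at least 35 to 40.

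Assumptions:
- true agreement p1 on the old wording and p2 on the new;
- independent rounds of equal size;
- answers reduced to agree or not agree;
- uncorrected 2×2 chi-square.

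With a and b agreeing in the two rounds,

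χ² = 2n·[a(n−b) − b(n−a)]² / [n·n·(a+b)·(2n−a−b)], 1 degree of freedom.

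The probability of closing is the sum, over all pairs (a, b) with p≥0.05 and b ≥ r, of Bin(a; n, p1)·Bin(b; n, p2). Here r is the smallest count that reaches 75%: 23 of 30, 27 of 35, 30 of 40. The stricter version also requires a ≥ r.

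| Old → new agreement | n | P(p≥0.05) | and new wording ≥75% | and both rounds ≥75% |
|---|---|---|---|---|
| 60% → 80% | 30 | 0.61 | 0.38 | 0.033 |
| | 35 | 0.55 | 0.32 | 0.019 |
| | 40 | 0.50 | 0.36 | 0.029 |
| 70% → 80% | 30 | 0.86 | 0.62 | 0.21 |
| | 35 | 0.84 | 0.59 | 0.17 |
| | 40 | 0.82 | 0.66 | 0.26 |

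**A single case.** Take 22 of 40 (55%) on the old wording and 30 of 40 (75%) on the new. Then χ² = 80·(22·10 − 30·18)² / (40·40·52·28) = 3.52 and p = 0.061. Under the Abstract's rule, the new text is stable consensus after one vote. If both rounds had to reach 75%, this case would be excluded, since 55% is below the threshold.

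**The case against.** **The comparison is not stated.** No section says that a reworded item is tested against its old text. The two consecutive rounds in 2.6 can be read as two rounds on the same statement, and that reading would remove the problem. This stands as a limit on the point: the text permits the comparison but does not prescribe it. It does not dispose of the point, because 2.4.4 explicitly puts revised items under the same closing rule as the rest. Nor is this only a detail left to a fuller document, since the article itself states the test, its start and the path of revised items.

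**Consensus may be needed in both rounds.** The 2.6 sentence on consecutive rounds can also be read this way. The problem then shrinks a great deal for a large wording effect (0.02 to 0.03 for 60% to 80%) and less for a smaller one (0.17 to 0.26 for 70% to 80%). What remains are items that had at least 75% support under each wording, where the harm is smaller.

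**There are other safeguards.** Rounds continue until at most 10% of panellists give feedback that calls for further adjustment (2.4.4), and panellists may comment on the final statements before publication (2.4.5). Both reduce the consequence. Neither requires a second vote on the revised text.

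**The calculation is simplified.** Kruskal–Wallis on 7-point scores would behave differently from an agree/not-agree chi-square, and the test's low power affects unrevised items too. Both are true, so the figures are illustrative only.

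**A stronger reading that the figures do not support.** A reader might take the test's low sensitivity as the error rate. If rewording lowered true agreement from 77% to 57%, the test would give p≥0.05 with probability 0.63, 0.56 and 0.53 at n = 30, 35 and 40, which suggests wrong closure more than half the time. But closing also needs 75% or more. With that condition the probability of closing as stable agreement is 0.021, 0.011 and 0.014, about 1–2%.

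**Conclusion.** The point holds as a gap in the stated rule: sections 2.4.4 and 2.6 together permit a substantively reworded statement to be closed as stable after a single vote on its final wording. A reader might infer that the plan requires new wording to be tested against old. The article does not say so, and that comparator is only deduced from testing that begins in round 2.

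The size depends on how 2.6 is read. If only the current round must reach 75%, closure after one vote has probability 0.32–0.38 for a lift from 60% to 80% and 0.59–0.66 for 70% to 80%. If both rounds must reach it, the figures are 0.02–0.03 and 0.17–0.26. All of them rest on assumed agreement rates, independent rounds, a dichotomised chi-square and the Abstract's p-value rule.

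The gap does not depend on which p-value direction is meant. Under 2.6 as printed, a rewording that shifted the answers significantly would count as stable. The two directions conflict in any case, and the test cannot be applied until one is chosen. The change is worth making, because section 2.8 places round 1 still ahead and the cost is small.

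**What to change.** Add to sections 2.4.4 and 2.6:

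- Stability is tested only between rounds in which the statement had identical wording.
- A substantively reworded statement is treated as new. Its stability count restarts, and it can close only after two votes on its final text.
- The steering committee classifies and logs each edit as substantive or not before that round's results are seen. Non-substantive edits do not restart the count.

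State also whether one or both rounds must reach 75%, and give the same p-value direction in the Abstract and in 2.6.

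The cost is a few sentences and, for statements revised late, up to one more round. A round lasts 2 weeks (section 2.3), against a planned 12 to 15 months (section 2.2).

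### Dissensus is defined only by the ≥75% threshold, so a statement that settles on a split has no defined outcome, and the closing rules conflict on whether it closes

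*Protocol article*

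**What the plan says.** **Outcome definitions.** The Abstract says: "Consensus will be deemed achieved when a choice in MCQs or a Likert-scale statement achieves ≥75% agreement or disagreement". Section 2.4.4 continues statements "until a stable consensus or dissensus is reached (defined as ≥75% agreement or disagreement on a Likert scale and selected options in an MCQ". Section 2.6 says: "Consensus will be defined when a choice in the MCQ or Likert-scale question has at least 75% of the votes from panellists". It groups Likert scores 1–3 as disagreement, 4 as neutral and 5–7 as agreement. No sentence defines dissensus on its own.

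**When stability is examined.** Section 2.6 gives two statements: "The stability of the responses will be analyzed from the second round onwards using the non-parametric Chi-square test or Kruskal–Wallis test" and, later in the same paragraph, "Stability is assessed after two consecutive rounds of answers defined as consensus or dissensus".

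**When the rounds stop.** The Abstract says: "Rounds will continue until stability is achieved for all statements". Section 2.4.4 ends with "The Delphi rounds will continue until the responses stabilize, with no more than 10% of panellists providing feedback that requires further adjustments" and "The process will be repeated until stability is achieved for all statements". The strengths paragraph of the Discussion also makes stability across all statements the endpoint. None of these sentences mentions 75%.

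**Direction of the test.** The Abstract takes p ≥ 0.05 as stable. Section 2.6 takes p ≥ 0.05 as a lack of stability.

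**The concern.** Section 2.4.4 attaches one criterion, ≥75%, to both consensus and dissensus. Because the Abstract already treats ≥75% disagreement as a form of consensus, dissensus is left either as another name for consensus against a statement or with no content. A panel that settles with no class at 75%, which is what dissensus ordinarily means, falls under neither term. The gap is plainer for an MCQ, which has no disagreement side.

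The later sentence of section 2.6 makes the gap operational. If stability is assessed only after two consecutive rounds classed as consensus or dissensus, and both need 75%, a settled split is never assessed. Other sentences say that it is.

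The first part of the Discussion gives clarifying areas of agreement and of disagreement as an aim, and section 2.4.5 is headed as the step where final consensus or dissensus is stated. The Introduction describes low-level evidence and widely varying practice, so split statements are to be expected. Whether such a split is closed and reported as disagreement, polled again, or revised or removed by the steering committee should not be decided after the votes are seen.

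**Working it through.** The article gives no calculation on this point, so there is no figure to reproduce. The check applies each sentence to one example. The split is an assumption, because the article gives none.

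**Inputs.** Panel of 40, the upper end of the range in the Abstract and in section 2.3; threshold 75% (Abstract, 2.4.4, 2.6); three Likert classes (2.6). Assumed votes: 20 agree, 4 neutral, 16 disagree.

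**Step 1: votes needed.** 0.75 × 40 = 30.

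**Step 2: classify.** 20/40 = 50% agree, 4/40 = 10% neutral, 16/40 = 40% disagree. No class has 30 votes. By the Abstract and section 2.6 this is not consensus. By the parenthesis in section 2.4.4 it is not dissensus either. An MCQ with three options voted 20/4/16 gives the same result.

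**Step 3: test round to round.** The chi-square statistic is Σ(O − E)²/E with (2 − 1)(3 − 1) = 2 degrees of freedom, for which p = exp(−χ²/2).
- Same votes in the next round: χ² = 0, p = 1.00. Kruskal–Wallis also gives p = 1.00.
- One panellist moves from disagree to agree (21/4/15): the expected counts per round are 20.5, 4 and 15.5, so χ² = 2 × 0.25/20.5 + 0 + 2 × 0.25/15.5 = 0.0244 + 0.0323 = 0.0567, and p = exp(−0.0283) = 0.97. Kruskal–Wallis with the classes ranked in order gives p = 0.81.

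**Step 4: apply each rule to the unchanged split.**

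| Text followed | Tested? | Closes? |
|---|---|---|
| Definition in 2.4.4 with the two-consecutive-rounds sentence of 2.6 | No, because it is neither consensus nor dissensus | No |
| Round-2-onwards sentence of 2.6, stability-only stopping, p-value direction of the Abstract | Yes, p = 1.00 | Yes, at round 2, if the 10% feedback condition of 2.4.4 is also met |
| As above, p-value direction of 2.6 | Yes, p = 1.00 | No, because p = 1.00 is labelled a lack of stability |

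The same votes give opposite results according to the sentence followed. The third row shows that defining dissensus is not enough while the p-value direction is unresolved.

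**The case against.** The best defence is that dissensus is simply the complement of consensus. Section 2.6 applies the 75% rule to consensus alone, and it says that the reported results will show the degree of consensus or dissensus for each statement, which implies that every statement falls into one class or the other. On that reading the two-consecutive-rounds sentence covers every statement, including a split MCQ. This reading is workable and may be the intended one. It does not remove the point, because the parenthesis in section 2.4.4 says something different and nothing tells the committee which governs.

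Stronger conclusions are tempting but not supported:

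- A reader might infer that the Delphi can never end while one statement is split. The Abstract, the last sentences of section 2.4.4 and the Discussion allow stopping on stability, which a settled split can meet under the Abstract's p-value direction.
- A reader might infer that removal by the committee is the only way out, so that disagreement is selectively deleted. Section 2.4.4 also allows revision and ties changes to panel feedback and responses. Section 2.6 promises final percentages for every answering option, so a retained split would be visible.
- A reader might want a probability that a split statement reaches 75%, treating each round as a fresh binomial draw. The same panellists are polled again, so independent draws do not describe the process, and the answer would only restate that a statement well below 75% tends to stay there.
- A reader might see the absence of a maximum number of rounds as an error. Stopping on stability is the stated design, with two-week rounds and a project of 12 to 15 months, so a cap is optional.

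**Conclusion.** The point holds as an undefined outcome combined with conflicting closing rules. Sections 2.4.4 and 2.6, read together, leave a settled split without a category, without a stability test and without closure. Other sentences in section 2.6, the Abstract, section 2.4.4 and the Discussion would test it from round 2 and let it close. This is a fault in rules that the article prints, not detail left to a fuller document.

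The effect on any one split statement is all or nothing, as the 20/4/16 example shows: closed at round 2 or not closed. The number of statements affected cannot be estimated, because section 2.8 shows that statements were still being formulated and round 1 had not begun. The example rests on an assumed split and an assumed full response of 40. The conflict itself does not depend on either; it arises for any settled distribution with nothing at 75%.

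**What to change.** Before round 1:

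1. Define three outcomes in sections 2.4.4 and 2.6 and in the Abstract: **consensus-agree** (≥75% scoring 5–7, or ≥75% for one MCQ option); **consensus-disagree** (≥75% scoring 1–3, Likert only); **stable dissensus** (none of these reached, and responses stable between two consecutive rounds of the same wording).
2. Delete the sentence in section 2.6 that makes the stability assessment depend on two rounds of consensus or dissensus.
3. State that every statement is tested from round 2 and is closed once stable, whichever outcome it has.
4. State that a statement is not removed only because it lacks consensus.
5. Give the p-value rule the same direction in the Abstract and in section 2.6. Without this, the other changes cannot operate.

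A maximum number of rounds may be added but is not needed for consistency.

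The cost is a few sentences, with no change to the panel or questionnaire format. The small downside is that some statements will be reported as unresolved, which fits the stated aim of showing where experts disagree.
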